### Bioefficacy studies and chemical analysis with cohort 2 nets

Nets belonging to cohort 2 will be randomly selected per arm for bioefficacy studies and chemical analysis. Nets of each type (Interceptor^®^ G2, Royal Guard^®^ and Interceptor^®^) will be destructively sampled from households at 6, 12, 18-, 24-, 30- and 36-months post-distribution and replaced with new nets of the same type at each sampling point. They will be subjected to laboratory bioassays (WHO cone bioassays and tunnel tests where necessary) and experimental hut trials to monitor entomological efficacy against mosquito vectors and to chemical analysis to monitor changes alphacypermethrin, chlorfenapyr and pyriproxyfen content. For laboratory bioassays, net pieces measuring 30cmx30cm will be cut from each net following WHO guidelines [13]. Nets withdrawn at annual time points (12, 24 and 36 months) will be tested in experimental huts before laboratory bioassays. The number of whole ITNs of each type to be subjected to each type of study at each timepoint is summarized in Table 1 below.

**Table 1 Tab1:** Number of Interceptor^®^ G2, Royal Guard^®^ and Interceptor^®^ ITNs to be sampled from Cohort 2 at each timepoint

Months post ITN distribution	No of ITNs to withdrawn for bioefficacy studies	No. of ITN to test in hut trials	No. of ITNs to test in lab bioassays	No. of pieces per ITN	Total number of pieces for bioassays	No. of pieces for chemical analysis^b^	ITNs sampled for other studies^c^	
0	30	–	30	5	150	150		
6	30	–	30	4	120	–		
12	54^a^	54^a^	30	4	120	120	80	
18	30	-	30	4	120	-		
24	54^a^	54^a^	30	4	120	120	80	
30	30	–	30	4	120	–		
36	54^a^	54^a^	50	4	200	200	80	
Total	282				950	590	240	

^a^These nets will be tested in hut trials prior to laboratory bioassays and chemical analysis. Hut trials will only be performed with nets withdrawn at 12, 24 and 36 months

^b^Net pieces preserved for chemical analysis will be obtained from adjacent positions on the same ITNs cut for bioassays

^c^These nets will be samples from cohort 2 nets but will be used in other studies

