#### Laboratory bioassays and strain selection

Cone bioassays and tunnel tests will be performed at the CREC-LSHTM GLP-certified facility to monitor the bioefficacy of each active ingredient in each ITN brand using ITN pieces obtained from field collected nets at each time point. Current WHO ITN durability guidelines were tailored towards pyrethroid-only nets and therefore do not describe methods for assessing the bioefficacy of non-pyrethroid chemicals on ITNs [13]. Unlike pyrethroids that require a pyrethroid-susceptible *Anopheles* strain for durability bioassays, evaluation of the insecticidal activity of chlorfenapyr in Interceptor^®^ G2 and pyriproxyfen in Royal Guard® will require the use of a pyrethroid-resistant strains that is susceptible to these insecticides to reduce any confounding effects from the pyrethroid component.

Following a series of preliminary laboratory bioassays, the pyrethroid resistant *An. coluzzii* Akron strain (BEI resources) maintained at the CREC-LSHTM insectary since 2018 was identified as a suitable strain for monitoring the bioefficacy of chlorfenapyr and pyriproxyfen in Interceptor^®^ G2 and Royal Guard^®^ ITNs from the trial. Preliminary WHO susceptibility bottle bioassays [28, 29] performed with alpha-cypermethrin (12.5μg), chlorfenapyr (100μg) and pyriproxyfen (100μg) showed that the strain was resistant to pyrethroids but susceptible to chlorfenapyr and pyriproxyfen (Fig. 3). Mortality with deltamethrin in WHO tube assays increased from 19 to 77% demonstrating the partial involvement of mixed function oxidases in pyrethroid resistance in the Akron strain. Dissection of ovaries of blood-fed *An. coluzzii* Akron mosquitoes exposed to pyriproxyfen treated bottles revealed a 98% reduction in mosquito fertility relative to unexposed mosquitoes thus showing susceptibility to pyriproxyfen. The WHO cone bioassays performed with Akron mosquitoes using unwashed and washed pieces of the pyrethroid-only ITN (Interceptor^®^) showed high survival (> 60%) demonstrating that the impact of chlorfenapyr and pyriproxyfen in Interceptor^®^ G2 and Royal Guard^®^ will be less confounded by the alphacypermethrin component in these nets when tested in laboratory bioassays using this strain.

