**Fig. 3 Fig3:**
[figure not shown]
Susceptibility of the pyrethroid-resistant *Anopheles coluzzii* Akron strain to insecticides in study nets. Chlorfenapyr, pyriproxyfen and alpha-cypermethrin exposures were performed in WHO bottle bioassays while deltamethrin exposures were performed in WHO filter paper tube tests. Approximately 100 mosquitoes of each strain were exposed for 1 h to each insecticide in replicates of 25. For pyriproxyfen, mosquitoes were blood-fed before exposure and their ovaries dissected after 72 h to assess ovary development

Based on results from these preliminary bioassays, the testing plan in Table 2 will be used in laboratory bioassays for monitoring the bioefficacy of each active ingredient in the different ITN brands in the trial. In line with WHO guidelines, ITN bioefficacy at each timepoint will be expressed in terms of the proportion of ITNs passing the efficacy criteria for each active ingredient in cone bioassays or tunnel tests.

**Table 2 Tab2:** Summary of laboratory bioassay methodology and outcome measures for assessing the insecticidal durability of Interceptor^®^ G2 and Royal Guard^®^ in Benin compared to Interceptor^®^

ITN type	Brand name	Active ingredient	Mosquito strain	Mosquito age and status (N)	Primary test method (exposure time)	Key outcome measures	ITN efficacy criteria	Remarks/additional tests
Pyrethroid-only	Interceptor	alpha-cypermethrin	Susceptible *An. gambiae* s.s. Kisumu	unfed, 3–5 days old (40–50/net)	cone bioassays (3 min)	Knockdown, 24 h Mortality	knock-down ≥ 95% or mortality ≥ 80%	Tunnels for failed nets
Pyrethroid-chlorfenapyr	Interceptor G2^a^	alpha-cypermethrin	not tested	not tested	not tested	not tested	not tested	not tested due to lower dose of pyrethroid
		chlorfenapyr	Pyrethroid-resistant *An. coluzzii* Akron	unfed, 5–8 days old (100/net)	Tunnel tests (overnight)	72 h Mortality and Blood-feeding inhibition	Mortality ≥ 80% or Blood-feeding inhibition ≥ 80%	1 net piece per ITN
Pyrethroid- pyriproxyfen	Royal Guard	alpha-cypermethrin	Susceptible *An. gambiae* s.s. Kisumu	unfed, 5–8 days old (40–50/net)	cone bioassays (3 min)	Knockdown, Mortality	knock-down ≥ 95% or mortality ≥ 80%	Tunnels for failed nets
		pyriproxyfen	Pyrethroid-resistant *An. coluzzii* Akron	blood-fed, 5–8 days old (80–100/net)	cone bioassays (3 min) plus ovary dissection after 72 h	% reduction in fertility relative to control^b^	Reduction in fertility relative control	> 30% fertility required in control

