^a^For Interceptor G2, given the low dose of alpha-cypermethrin, chlorfenapyr bioefficacy will be prioritised

^b^Mosquitoes presenting with Christopher stage V ovaries, will be considered fertile

Alpha-cypermethrin bioefficacy in Royal Guard^®^ and Interceptor^®^ will be assessed using the susceptible *An. gambiae* Kisumu strain in 3 min cone bioassays following current WHO protocols. At each timepoint, 40–50 unfed 3–5 days old *An. gambiae* Kisumu mosquitoes will be exposed to each whole Royal Guard^®^ and Interceptor^®^ ITN in replicates of 5 mosquitoes per cone and 2 cones per ITN piece. ITNs which fail to achieve WHO efficacy criteria in these cone bioassays (pooled knock-down ≥ 95% or pooled 24h mortality ≥ 80%) will be subjected to tunnel tests. For each ITN that failed in cone bioassays, only one ITN piece (with cone bioassay mortality that is closest to the mean) will be tested in tunnels. Approximately 100 unfed 5–8 days old susceptible *An gambiae* Kisumu will be exposed to each ITN piece in the tunnel tests and efficacy of alpha-cypermethrin in Interceptor^®^ and Royal Guard^®^ will be measured in terms of mortality after 24h (≥ 80%) or blood-feeding inhibition (≥ 90%).

Given the relatively low concentration of alpha-cypermethrin in Interceptor^®^ G2 (100 mg/m^2^), bioefficacy studies performed with the net will focus more on its chlorfenapyr component. The unsuitability of cone bioassays for assessing the efficacy of chlorfenapyr on ITNs has been demonstrated in several studies [19, 30] hence only tunnel tests will be used for evaluating the activity of chlorfenapyr in Interceptor^®^ G2 with the pyrethroid-resistant Akron strain. To improve the efficiency of the tunnel test bioassays, only 1 ITN piece per whole Interceptor^®^ G2 will be tested in tunnels. A total of ~ 100 unfed 5–8 days old pyrethroid resistant *An coluzzii* Akron will be exposed overnight in each tunnel test with Interceptor^®^ G2 and efficacy in tunnels will be measured in terms of mosquito mortality after 72h (≥ 80%) or blood-feeding inhibition (≥ 90%).

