### Statistical analysis

Data from the surveys at 6, 12, 24, and 36 months will be used to calculate attrition, functional survival and median survival time using Kaplan–Meier estimators. For functional survival, nets reported as given away, sold, or stolen will be excluded from the analysis. Negative binomial regression will be used to compare hole surface area between the different ITN types. Data on WHO cone bioassays and tunnel tests will be obtained from 30 nets of each product type sampled at each time point. A chi-squared test will be used to assess the proportion of nets of each ITN type passing the WHO criteria for alphacypermethrin, chlorfenapyr and pyriproxyfen bioefficacy based on combined cone and tunnel tests. Proportional outcomes (mortality, blood-feeding, exophily) from the experimental hut trials will be compared at each time point using mixed effects logistic regression, with huts, sleepers, net replicate and nightly observational error included as random or fixed effects [33]. Numerical outcomes (hut entry) will be compared using negative binomial regression. A separate model will be fitted for each outcome to determine whether there is (i) a significant change over time, and (ii) a significant difference between ITNs washed 20 times and 36-month-old naturally aged ITNs. Analysis will be performed on STATA or the package *lme4* of the R software.

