Current WHO ITN evaluation guidelines define specific thresholds for determining the efficacy of ITNs in insecticidal durability bioassays. Nets that induce ≥ 95% knockdown and/or ≥ 80% mortality in cone bioassays or ≥ 80% mortality and/or ≥ 90% blood feeding inhibition in tunnel tests are considered efficacious. While proposing these same efficacy criteria for the laboratory bioassays for alpha-cypermethrin and chlorfenapyr bioefficacy in the study nets, it is recognized that these cut-offs were primarily developed for fast-acting pyrethroid insecticides on nets and may need to be modified for non-pyrethroid insecticides. Indeed, new draft WHO guidelines proposed for ITN prequalification aim more for a weight of evidence approach and do not allude to specific efficacy thresholds [39]. The weight of evidence approach may be suitable for assessing individual ITN products but could be challenging for comparing between ITN product brands and making programmatic and procurement decisions, which is usually the main objective for ITN durability studies. Efficacy criteria for the sterilizing effects of pyriproxyfen on ITNs are yet to be defined in WHO guidelines. Further studies investigating correlations between the sterilizing effects of Royal Guard^®^ nets in laboratory bioassays and their epidemiological performance against clinical malaria in the current trial, may contribute towards the identification of a suitable cut-off for the impact of pyriproxyfen in ITN durability studies.

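### The only laboratory analysis of chlorfenapyr activity reduces each Interceptor G2 tunnel test to pass/fail and applies a chi-squared test, which can lose much of the power to detect decline with net age

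*Protocol article*

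**What the plan says.** The text introducing Table 2 (Laboratory bioassays and strain selection) says that bioefficacy at each time point will be "expressed in terms of the proportion of ITNs passing the efficacy criteria for each active ingredient". The Statistical analysis section adds: "Data on WHO cone bioassays and tunnel tests will be obtained from 30 nets of each product type sampled at each time point". It then names the test: "A chi-squared test will be used to assess the proportion of nets of each ITN type passing the WHO criteria". It does not say which groups or time points are compared. Table 1, under "No. of ITNs to test in lab bioassays", gives 30 nets at every time point except 36 months, where it gives 50.

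Tunnel tests are the only laboratory method for chlorfenapyr, with "only 1 ITN piece per whole Interceptor" G2 net and about 100 Akron mosquitoes per test. Efficacy is "measured in terms of mosquito mortality after 72h" (at least 80%) or as blood-feeding inhibition. The inhibition cut-off is 90% in the text and 80% in Table 2.

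On the status of these cut-offs, the article says that current WHO durability guidelines "do not describe methods for assessing the bioefficacy of non-pyrethroid chemicals on ITNs". The Discussion concedes that "these cut-offs were primarily developed for fast-acting pyrethroid insecticides on nets and may need to be modified for non-pyrethroid insecticides".

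For the hut trials, the Statistical analysis section models mortality by mixed-effects logistic regression and adds models for change over time.

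**The concern.** About 3,000 mosquito outcomes per time point (30 × 100) become 30 yes/no values. Where mean mortality sits well above 80%, most nets pass before and after a decline. Where it sits well below, most fail before and after. What the test sees then depends on how close the mean lies to 80%, more than on how much activity was lost.

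The second study objective is to follow insecticidal activity over three years, and the Discussion treats monitoring the non-pyrethroid component by bioassay as essential. Chlorfenapyr is in one trial product only. Under Table 2, the other products' pass rates come from different primary tests, and for alpha-cypermethrin from a different strain. The informative contrast is therefore Interceptor G2 against itself over time, which is where the lost power matters. A real decline in the tunnel test could be reported as no significant change.

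**Working it through.** **Inputs from the article.** 30 nets per time point (50 at 36 months, Table 1); about 100 mosquitoes per net; mortality cut-off 80%. The article states no power, effect size or between-net variation for the bioassays, so there is no figure to reproduce. Its only power target (80%) is for hut superiority of new unused nets.

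**Assumptions.** Two-sided 5% level. Each net's true mortality is normal on the logit scale, centred so that the average over nets equals the stated mean. Between-net SD varies over a range. Clustering is ignored.

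**Step 1: what chi-squared can detect.** With p̄ the average of the two pass proportions, power = Φ{[|p1 − p2| − 1.96√(p̄(1 − p̄)(1/n1 + 1/n2))] / √(p1(1 − p1)/n1 + p2(1 − p2)/n2)}. For 95% v 67% passing and 30 v 30 nets: p̄ = 0.81; (0.28 − 1.96 × 0.1013)/0.0946 = 0.86; power = 0.80. From 90% the pass rate must fall to about 59%, and from 80% to about 46%. With 30 v 50 nets the figures are 95→70%, 90→63% and 80→49%.

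**Step 2: what a decline does to the pass rate.** With SD 0.6, mean mortality of 95% gives about 100% of nets passing and 90% gives about 93%. Survivors double, from 5% to 10%, yet the pass rate moves only 7 points.

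**Step 3: power on the same simulated data.** Deaths are Binomial(100, p). Chi-squared on nets with at least 80 deaths is compared with a t-test on net-level logit mortality, 30 v 30 nets.

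| Mean mortality | Chi-squared, SD 0.5 / 0.8 / 1.2 | Net-level, SD 0.5 / 0.8 / 1.2 | Loss (points) |
|---|---|---|---|
| 95→90% | 5 / 25 / 29% | 99 / 89 / 66% | 94 / 64 / 37 |
| 90→80% | 97 / 81 / 58% | 100 / 96 / 83% | 3 / 15 / 25 |
| 85→75% | 95 / 70 / 46% | 99 / 88 / 64% | 4 / 18 / 18 |
| 75→65% | 67 / 47 / 32% | 93 / 69 / 45% | 26 / 22 / 13 |
| 65→50% | 32 / 52 / 41% | 100 / 90 / 71% | 68 / 38 / 30 |

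With 50 nets at 36 months and SD 0.8: 95→90% gives 24% v 95%, 85→75% gives 80% v 93%, and 65→50% gives 59% v 95%.

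**Step 4: trend over 0, 6, 12, 24 and 36 months** (30, 30, 30, 30 and 50 nets; SD 1.0). Five-group chi-squared v regression of logit mortality on age: 95→90%, 25% v 94%; 90→80%, 71% v 99%; 85→75%, 55% v 93%. Part of this gap comes from ignoring time order. A trend test on the pass rates gives 51%, 89% and 79%, so the rest is due to the cut itself.

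**Step 5: the either/or rule.** Step 3 uses mortality alone. With SD 0.6, mean inhibition held at 85% and correlation 0.5, power for 90→80% falls from 93% (mortality only) to 82% with the 90% inhibition cut, or 33% with the 80% cut. Net-level mortality gives 100%. At mean inhibition of 92% the figures are 38% and under 1%. If inhibition also declined with age, the loss would be smaller.

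**Step 6: false positives.** Without variation between bioassay rounds, both tests hold near 5%. Adding round-to-round variation (assumed logit SD 0.2) raised the net-level test to about 20% and chi-squared to about 11%. The net-level gain is valid only if round is accounted for.

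**The case against.** Four points have force.

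- **The tunnel test is not the only evidence on ageing nets.** At 12, 24 and 36 months, 54 field-aged Interceptor G2 nets go into huts against a vector population that resists pyrethroids but is susceptible to chlorfenapyr. Mortality at 72 h is modelled without a cut, and chlorfenapyr content is assayed at 0, 12, 24 and 36 months. A reader might infer that the plan could not detect a decline in this net's killing effect. The documents do not support that. What remains is that huts test both ingredients together, whereas the Akron tunnel test was chosen to limit the pyrethroid's contribution.
- **Pass/fail is a reasoned choice.** The Discussion defends thresholds for comparing brands and for procurement. That justifies reporting the pass rate. It does not make the pass rate a good test of change within one product.
- **The article may be condensed.** Table 2 lists 72 h mortality and blood-feeding inhibition as outcome measures, and an unseen plan may model them. But the article itself fixes the summary measure and names the test. Its sentence on change over time follows the hut outcomes and does not clearly cover tunnel data.
- **The size depends on assumptions.** A reader might infer that most of the power is always lost. In Step 3, chi-squared loses more than half the comparator's power in only 4 of 15 cells: 95→90% at all three SDs, and 65→50% at SD 0.5. The comparator is also a simple t-test without cluster or round effects, so figures near 100% are probably optimistic for the recommended model.

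**Conclusion.** The concern holds for the laboratory analysis of chlorfenapyr. Reducing each tunnel test to pass/fail and comparing 30 nets per time point can lose much of the power to detect decline. The loss is largest when mean mortality stays well to one side of 80% (95→90%: about 5-29% v 66-99%). It is smaller, about 3-25 points, when the decline reaches or crosses 80%. The either/or rule can add to the loss where many nets pass on blood-feeding inhibition. Mean mortality, between-net SD and feeding inhibition are assumed, because the article gives none of them. The direction is consistent across the 30 v 30 scenarios tabulated, but the size is not fixed. This is a worthwhile improvement to the analysis. It does not invalidate the study, and it is no reason to drop the pass rate.

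**What to change.** 1. Keep the proportion of nets passing as the reported WHO-style indicator.
2. For Interceptor G2, add as the test of change over time a mixed-effects logistic regression of 72 h tunnel mortality on net age, and a separate one for blood-feeding. Use random effects for net and cluster. Account for bioassay round through the new unused Interceptor G2 net that the article already tests alongside.
3. State that conclusions on loss of chlorfenapyr activity in the tunnel test rest on this model.
4. Say which groups and time points the chi-squared test compares.
5. Reconcile the blood-feeding inhibition cut-off (80% in Table 2, 90% in the text after it) and the number of nets at 36 months (30 in Statistical analysis, 50 in Table 1).

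The cost is wording and some extra analysis. No further field nets are needed: each test already yields deaths among about 100 mosquitoes, and the method is already named for the hut data. The one dependency is enough new-net replicates in each round to estimate the round effect. If there are too few, the model's precision or its type I error will suffer.

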### Study design

The study area was divided into 60 clusters that were randomly assigned to the three arms of the cRCT using restricted randomization. Study nets are identical in appearance and participating households are blinded to the type of ITN they received. Field data collectors are also blinded to the allocation of households to the study arms. Ten clusters from each study arm have been randomly selected for the durability assessment (Fig. 1). Following ITN distribution, households in these clusters will be visited to mark and prospectively follow 2 separate cohorts of ITNs per arm (Cohorts 1 and 2) every 6–12 months to monitor their physical and insecticidal durability over a period of 36 months. Cohort 1 will consist of at least 750 nets from ~ 250 randomly selected households per arm (assuming 3 ITNs are distributed per household) from 5 study clusters per study arm. These nets will be followed for ITN survivorship and fabric integrity at 6-, 12-, 24- and 36-months post ITN distribution. Cohort 2 will consist of ~ 1800 nets per study arm from ~ 600 households from all 10 randomly selected clusters (60 households per cluster) per study arm to be withdrawn (and replaced with new nets) for assessment of insecticidal activity in laboratory bioassays and experimental hut trials, content of each active ingredient and for other studies. Cohort 1 and cohort 2 nets will receive separate identification numbers and would be sampled from different households to prevent the risk of destructive sampling of nets intended for ITN survivorship studies (cohort 1). Figure 2 provides a summary of the study design and studies to be performed at each timepoint.

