### Sample size calculations

Sample size calculations are performed based on previous ITN durability data from Benin. For cohort 1, a sample size of 750 nets of each brand from 250 randomly selected households (assuming ~ 3 ITNs are distributed per household) in 5 study clusters was found sufficient to detect a 9.4% absolute difference (hazard ratio = 0.87) in ITN attrition rate assuming an attrition rate in the control arm of 70% over the 3 years and an intra-cluster correlation coefficient of 0.03. For cohort 2, a total of 522 ITNs will need to be withdrawn over three years and assuming a loss rate of 70% a total of 1800 ITNs will be marked per study arm at baseline. To reduce the impact of the durability study on the outcomes of the cRCT, cohort 2 nets will be obtained from households in the buffer areas of the selected clusters to exclude the core areas used for the cRCT sampling.

For each experimental hut trial and at each timepoint, data on the number of mosquitoes per night and the magnitude of the different random effects (huts, sleepers, nights and observational error) will be reviewed after the first round of 9 or 13 weeks and power calculations conducted by simulation using previously described methods [33]. Power analysis will determine whether the hut trial has a desired 80% power to detect superiority in mosquito killing of any new unused dual AI ITN over the new unused pyrethroid-only net, assuming a true underlying extra mortality from the dual AI net of 40%. A second round of hut trial would be performed if the desired level of power is not achieved.

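### The bioassay pass rates come from a cluster-allocated design with 10 clusters per arm, but the named chi-squared test treats nets as independent: a small error at the only ICC given, larger at higher assumed ICCs, and free to correct

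*Protocol article*

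**What the plan says.** On allocation, Study design says: "The study area was divided into 60 clusters that were randomly assigned to the three arms of the cRCT using restricted randomization". The nets for bioassay (cohort 2) are drawn "from all 10 randomly selected clusters (60 households per cluster) per study arm". On selection, the section on bioefficacy studies says: "Nets belonging to cohort 2 will be randomly selected per arm for bioefficacy studies and chemical analysis". No fixed number per cluster is given.

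On numbers tested, Statistical analysis says: "Data on WHO cone bioassays and tunnel tests will be obtained from 30 nets of each product type sampled at each time point". Table 1 agrees up to month 30 but lists 50 nets at month 36.

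On the test, Statistical analysis says: "A chi-squared test will be used to assess the proportion of nets of each ITN type passing the WHO criteria". No cluster term or adjustment is mentioned, nor whether a continuity correction is used, nor whether the comparison is between net types or between time points.

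Dependence is recognised elsewhere. Sample size calculations use "an intra-cluster correlation coefficient of 0.03" for attrition in cohort 1, and the hut-trial outcomes are to be analysed with mixed models that carry hut, sleeper, net and night effects.

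**The concern.** A chi-squared test on net counts assumes that nets are independent. Nets from one cluster share a locality and probably similar washing and use habits, so their pass/fail results may be positively correlated. In a comparison between arms, net type varies only between clusters. Any positive correlation then makes the true variance of the difference larger than the test assumes, and its p-values come out too small.

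The share of nets passing is how the article expresses bioefficacy at each time point, and objective 2 compares the dual-ingredient nets with Interceptor. A difference in pass rate could therefore be declared with less evidence than its p-value suggests. The named test departs from the design, so this is not a detail merely left to a later analysis plan.

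**Working it through.** **Inputs.** From the documents: 10 clusters per arm; 30 nets per type per time point, or 50 at month 36 (Table 1); ICC 0.03 (attrition, cohort 1). Assumed, because not stated: two-sided 5% level, true pass rates of 60% and 80%, ICCs of 0.10 and 0.20 for pass/fail, and equal numbers per cluster (3 or 5).

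**The plan's own figure.** No sample size or power is given for the chi-squared test. The cohort 2 total can be checked: Table 1 gives 30 + 30 + 54 + 30 + 54 + 30 + 54 = 282 nets for bioefficacy, plus 240 for other studies, which makes 522. This matches "a total of 522 ITNs will need to be withdrawn over three years". Allowing for 70% loss, 522 / 0.30 = 1740, against 1800 marked (10 clusters × 60 households × 3 nets). The figure carries no allowance for clustering in the pass-rate comparison.

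**Design effect.** DE = 1 + (m − 1) × ICC, where m is the number of nets per cluster.
- 30 nets, m = 3: 1 + 2 × 0.03 = 1.06, so the effective number is 30 / 1.06 = 28.3.
- 50 nets, m = 5: 1 + 4 × 0.03 = 1.12, so the effective number is 50 / 1.12 = 44.6.

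**Approximate true error** of a nominal 5% test: 2 × [1 − Φ(1.96 / √DE)].
- DE 1.06 gives 5.7%.
- DE 1.12 gives 6.4%.
- A simple random draw within the arm leaves cluster counts unequal. DE is then 1 + ((n − 1)/10) × ICC, that is 1.087 and 1.147, and the error 6.0% and 6.7%.

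**Simulation, comparison between arms.** Beta-binomial clusters, 2 arms × 10 clusters, no true difference, 200,000 runs per setting, pass rate 80%:

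| Nets per type | ICC | DE | Uncorrected chi-squared | With continuity correction | t-test on cluster proportions |
|---|---|---|---|---|---|
| 30 | 0.03 | 1.06 | 5.6% | 2.7% | 4.8% |
| 30 | 0.10 | 1.20 | 7.3% | 3.7% | 4.8% |
| 30 | 0.20 | 1.40 | 9.8% | 5.3% | 4.9% |
| 50 | 0.03 | 1.12 | 6.6% | 3.8% | 4.9% |
| 50 | 0.10 | 1.40 | 10.1% | 6.3% | 4.9% |
| 50 | 0.20 | 1.80 | 15.0% | 10.2% | 4.8% |

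At a 60% pass rate the pattern is the same. With 50 nets, the corrected test gives 7.1% and 11.3% at ICC 0.10 and 0.20. The test on cluster proportions stays between 4.8% and 5.3% across both pass rates.

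**Simulation, time points within one net type.** The cluster effects are the same at both times and the pass rate is 80%. The uncorrected test gives about 4.7%, 4.0% and 3.2% with 3 nets per cluster at ICC 0.03, 0.10 and 0.20, and about 4.9%, 4.2% and 3.2% with 5. The shared cluster effect cancels from the difference, so the plain test becomes slightly conservative.

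**Which comparisons are affected.** In Table 2, chlorfenapyr is assessed only in Interceptor G2, pyriproxyfen only in Royal Guard, and alpha-cypermethrin only in Interceptor and Royal Guard. Two study arms meet on the same criterion only for alpha-cypermethrin.

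**The case against.** Several points can fairly be made for the plan, and most of them limit the finding.

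- **Size.** At the only ICC in the document the excess is about 1 to 2 percentage points. Part of this is the discreteness of the test: at a 50% pass rate and zero ICC it already gives about 5.2% (30 nets) and 5.7% (50 nets). A reader might infer gross inflation. The documents do not support that, because the 7–15% figures need assumed ICCs. Equally, 0.03 describes attrition, so it cannot show that the effect on insecticidal activity is negligible.
- **Version of the test.** The article does not say that the test is uncorrected. With a continuity correction the error stays below 5% at ICC 0.03. This stands, but with 50 nets the corrected test still reaches about 6–11% at ICC 0.10–0.20.
- **Direction.** The sentence on the test does not say what is compared. A reader might conclude that its p-values are always too small. For time points within a net type the opposite holds. The test misstates its error in either case, and objective 2 makes the comparison with Interceptor a stated aim.
- **Scope.** It would be wrong to read the problem as reaching every active ingredient in a between-arm comparison. Table 2 allows only one like-for-like contrast.
- **Households.** Shared households might seem to add a second layer of dependence. With about 600 households of 3 nets, a random draw of 30 from 1800 holds on average 435 × 2/1799 = 0.5 same-household pairs, and a draw of 50 holds 1225 × 2/1799 = 1.4. This is minor.
- **Month 36.** The inflation is largest with 50 nets, but that number stands only in Table 1, while Statistical analysis says 30 at each time point. The article does not say that the durability conclusion rests on this test, and superiority is also assessed in hut trials with mixed models.

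**Conclusion.** The point holds in limited form. The named test ignores the unit of allocation. In the alpha-cypermethrin comparison of Interceptor with Royal Guard, an uncorrected 5% test has a true error of about 5.6% with 30 nets per type and 6.6% with 50 at ICC 0.03, rising to about 7–10% and 10–15% at assumed ICCs of 0.10–0.20. A continuity correction removes the excess at ICC 0.03 but not, with 50 nets, at the higher values. For comparisons over time within one net type the test is slightly conservative, at about 3–5%.

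These figures assume a positive ICC for pass/fail, equal cluster counts, pass rates of 60–80%, and nets that were used in the field. Month-0 nets, if tested before distribution, would have no field clustering. The case for change rests on fit to the design and the absence of cost, not on a large error.

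**What to change.** Replace the chi-squared test with an analysis that respects cluster. Either of these would do:
- a test on the 10 cluster-level pass proportions per arm, which held its nominal level in every setting above;
- a logistic GEE or mixed model with cluster as the grouping unit and a small-sample correction.

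Use a permutation version, permuting whole clusters, when few nets fail. Keep cluster in the model for comparisons over time as well, so that the cancelling of shared cluster effects is used and not lost. State for each test whether it compares net types or time points, and on which active ingredient. Reconcile the 30 nets of Statistical analysis with the 50 of Table 1 at month 36.

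The cost is wording and analysis code. Cluster identity is part of the code marked on each net, so no further nets, assays or data are needed. The only downside is slightly larger p-values between arms. The status section reports bioassays still under way on nets withdrawn up to month 24, with complete data expected in 2024, so at the time of publication the change could still be made before the final analysis.
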